### Trial design {8}

TABASCO is an investigator-initiated, multi-center, randomized controlled trial testing whether postoperative treatment of chronic subdural hematomas using adjuvant drug therapy with tranexamic acid (test group) is equivalent to postoperative embolization of the MMA (control group) in terms of postoperative volume reduction of the hematoma and the need for revision surgery of CSDH within a follow-up period of 3 months. Eligible patients will be allocated in a 1:1 ratio to either the test or control group.

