### Outcomes {12}

#### Primary outcome

The primary element to be investigated in this study is the postoperative volume development of a primarily surgically relieved unilateral CSDH over the course of 3 months postoperatively. For diagnostic purposes and documentation, cranial cross-sectional imaging using native cMRI or CT-scan and subsequent volumetry to visualize the residual hematoma volume in milliliters will be performed at the planned follow-up time points, 1 day postoperatively, 1 week postoperatively, 1 month postoperatively, 2 months postoperatively and 3 months postoperatively. The volumetry will be performed by a radiologist who is not involved in the study. Although he is not informed about the group assignment of each patient, he is not blinded because the group assignment can easily be identified from the radiological evidence of the embolism material in the imaging. All findings are considered in relation to each other and in relation to the initial findings before the operation. The planned examination intervals correspond to the current standard of care for postoperative imaging follow-up after CSDH surgery and reflect the procedure used in comparable studies [27].

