**Fig. 2 Fig2:**
[figure not shown]
Preoperative volume measurement of a right-sided hemispheric chronic subdural hematoma using the CT data set

The following intervention-associated complications will be documented as part of the study:Vascular dissections caused by the guidewireDislocation of embolized materialIschemia caused by vascular occlusion during the interventionInflammation or abscesses at the puncture siteVascular fistula in the area of the puncture siteRetinal blindnessEpidural hematomas after perforation of the meningeal arteryAllergic reactions to the contrast mediumAcute renal failure

The following complications or adverse events associated with the use of tranexamic acid will be documented:Intolerance reactionsPulmonary embolismsVenous thrombosisEpileptic seizuresMyocardial infarctionsCerebral ischemic infarctionsAcute renal failure

All research data, including baseline data (NIHSS, mRS, hematoma volume, patient demographics and characteristics) prior to surgery, will be collected anonymously in an electronic data collection form at each study center. The PI of the trial summarizes these for all centers and exports data for statistical analysis. All investigators will be trained to perform outcome measurements and will be introduced to the data management prior to recruitment of the first patient.

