## Statistical methods

### Statistical methods for primary and secondary outcomes {20a}

The baseline data and outcome parameters are subjected to a simple descriptive data analysis (median, minimum, maximum and standard deviation in each case; mean only for metrically scaled characteristics).

For difference tests for nominal variables (gender, use of anticoagulation prior to surgery, occurrence of complications due to adjuvant therapy procedures, need for revision surgery), the Pearson chi-squared test is used.

For difference tests of ordinally scaled measured variables (NIHSS, mRS) within the respective groups at different points in time (linked samples), the data collected is tested for normal distribution using the Shapiro–Wilk test. In the case of a parametric distribution, the *t*-test is used for linked samples. In the case of a non-parametric distribution, the Wilcoxon test is used for connected samples (for two-group tests).

For the bivariate dependency analysis of the ordinal scaled characteristics between the two groups at the same point in time, the *t*-test for unconnected samples is used for a parametric distribution and the Mann–Whitney *U*-test for a non-parametric distribution after applying the Shapiro–Wilk test.

For metric variables (hematoma volume), which are subject to a normal distribution, the *t*-test for dependent samples is used to analyze the respective groups at different points in time. In the case of a non-parametric distribution, the Wilcox sign-rank test is used for the analysis.

For the bivariate dependency analysis of the metric characteristics between the two groups at the same point in time, after applying the Shapiro–Wilk test, the *t*-test for unrelated samples is used for a parametric distribution and the Mann–Whitney *U*-test for a non-parametric distribution.

In addition, a logistic regression is tested with the revision rate as the dependent variable and the treatment groups and baseline data as independent variables.

Furthermore, a correlation analysis of the relationship between the postoperative volume size and the revision rate as well as the postoperative neurological assessment and the revision rate is performed, in each case for mixed scaling pairs with the chi-squared test. The respective singular correlation analysis is followed by an analysis of the existence of a partial correlation between the two parameters in relation to the revision rate.

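### A Shapiro–Wilk pre-test picks the volume test afresh at each visit, so the primary comparison has no fixed effect measure, and no stated volume model uses the preoperative volume

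*Protocol article*

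**What the plan says.** The Primary outcome section makes the residual volume in millilitres over 3 months the primary element and lists five postoperative scans: "1 day postoperatively, 1 week postoperatively, 1 month postoperatively, 2 months postoperatively and 3 months postoperatively". It names no single primary time point and adds that "All findings are considered in relation to each other and in relation to the initial findings before the operation".

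Statistical methods {20a} sets the between-arm analysis of volume: "For the bivariate dependency analysis of the metric characteristics between the two groups at the same point in time, after applying the Shapiro–Wilk test". Data judged normal go to an unpaired t-test and all other data to Mann–Whitney. Neither branch is stated to be adjusted, and no effect estimate or interval is named for either. The ordinal scores (NIHSS, mRS) go through the same step.

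Volume before surgery is available. The data management section lists research data "including baseline data (NIHSS, mRS, hematoma volume, patient demographics and characteristics) prior to surgery". The only model described that relates treatment to an outcome with baseline data as covariates is for revision surgery, the secondary outcome: "a logistic regression is tested with the revision rate as the dependent variable and the treatment groups and baseline data as independent variables".

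Trial design {8} frames the aim as equivalence of tranexamic acid to embolization "in terms of postoperative volume reduction of the hematoma and the need for revision surgery of CSDH".

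**The concern.** Three things follow from letting a normality test choose the analysis.

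- **The estimand is not fixed.** A t-test targets a difference in means in mL. A Mann–Whitney test targets the ordering of the two distributions. The 1-month result could be one and the 3-month result the other, with no common scale for describing the time course that the primary objective asks about.
- **The rule has a gap.** It does not say what happens when one arm passes Shapiro–Wilk and the other fails.
- **Baseline information is left unused in the arm comparison.** If preoperative volume predicts later volume, an unadjusted test gives up precision that has already been paid for.

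This is text that the article states for its primary outcome, not a detail left to a fuller plan. Assessors cannot be blinded, so an analysis settled before outcome data are seen matters more than usual.

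**Working it through.** **1. The plan's own figure.** Rates 10% and 2%, two-sided alpha 0.05, power 0.80, pooled variance under the null (mean rate 0.06):

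n = [1.96·√(2·0.06·0.94) + 0.8416·√(0.10·0.90 + 0.02·0.98)]² / 0.08² = (0.658 + 0.279)² / 0.0064 ≈ 137.2, so 138 per arm, 276 in all.

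This reproduces (power 0.802 at 138). It concerns recurrence and gives no power for volume.

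**2. Inputs for volume.** From the protocol: 138 per arm, 1:1, alpha 0.05. It gives no volume SD, effect or correlation, so these are assumed: log-normal 3-month volume, log SD 0.7, log difference 0.22 (a ratio of e^0.22 ≈ 1.25), and baseline–outcome correlation ρ from 0 to 0.7.

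**3. Closed-form check.** Standard error = 0.7·√(2/138) = 0.0843, and 0.22/0.0843 = 2.61.

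- t-test on log volume: Φ(2.61 − 1.96) = 0.74.
- Mann–Whitney (relative efficiency 3/π on the log scale): Φ(2.61·√(3/π) − 1.96) = Φ(0.59) = 0.72.
- Log-scale ANCOVA: Φ(2.61/√(1−ρ²) − 1.96).

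| Analysis | ρ = 0 | 0.3 | 0.5 | 0.7 |
|---|---|---|---|---|
| ANCOVA, formula | 0.74 | 0.78 | 0.85 | 0.96 |
| ANCOVA, simulated | 0.72 | 0.77 | 0.85 | 0.95–0.96 |

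The planned rule was simulated as Shapiro–Wilk in each arm at 0.05, with a t-test if both pass and otherwise Mann–Whitney. It went to Mann–Whitney every time, with power 0.71–0.72. The unadjusted log t-test had 0.73–0.74, and a raw-scale t-test 0.63–0.65.

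**4. Splitting the loss.** From 0.71–0.72 to 0.73–0.74 is about 1–3 points: the cost of the rank test against the ideal scale. The further rise comes from adjustment, and at ρ = 0 there is none.

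**5. A second setting.** Take a standardised difference of 0.337, which gives an unadjusted t-test 80% power at 138 per arm. By formula, ANCOVA then has 83.6%, 89.9% and 97.5% at ρ = 0.3, 0.5 and 0.7. For 80% power it needs 126, 104 and 71 per arm. In simulation the planned rule had 78.8–79.1% with normal data and 76.7–78.6% with log-normal data.

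**6. Type I error.** The two-stage rule rejected in 4.7–5.4% of null simulations.

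**7. Instability of the choice.** With truly normal data, at least one arm fails with probability 1 − 0.95² = 0.0975 (simulated 9–11%). Over four independent visits the chosen test is mixed with probability 1 − 0.9025⁴ − 0.0975⁴ ≈ 0.34 (simulated 33%). Real visits are correlated, so this is only a guide. With mild skew, one arm passed and the other failed in 48–50% of trials at log SD 0.15, 41–43% at 0.20 and about 8% at 0.30.

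**8. Scale matters for the remedy.** At log SD 0.8, raw-scale ANCOVA was weaker than the planned rule: 70.4% against 77.8% at ρ = 0.3, and 74.3% against 76.7% at 0.5. Log-scale ANCOVA was stronger at each of the three correlations run (0.3, 0.5, 0.7).

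**The case against.** Much of the case on the other side stands.

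- **A reader might infer that the pre-test invalidates the test or causes the power loss.** Neither is supported. Type I error per comparison is held. With skewed volumes, switching to Mann–Whitney gains about 8 points over a raw-scale t-test. The loss comes from the missing adjustment.
- **The size rests on assumptions.** The protocol gives no volume SD, effect or correlation, and whether preoperative volume is a strong predictor is unknown. At a correlation near 0 nothing material is gained.
- **Instability and strong skew do not coincide.** If volumes are clearly skewed, the rule picks Mann–Whitney almost always and the measure is in effect constant. Switching arises mainly near normality, where it costs little power. But the measure is still known only after the data are seen.
- **A reader might infer that Mann–Whitney leaves no interval.** A Hodges–Lehmann shift in mL with its interval can accompany it. The article names none, but it names none for the t-test either.
- **A reader might infer that an interval would answer the equivalence question.** It would not without a margin.
- **Earlier volumes may not be ignored entirely.** The objective speaks of volume decrease and relates findings to the preoperative scan, so change may be the quantity tested. The text leaves this open. Change is no safe substitute: in the setting of step 5, with equal variances at both times, it has power 0.66, 0.80 and 0.95 at correlations 0.3, 0.5 and 0.7, below ANCOVA each time.
- **The one-arm-fails gap is minor.** The usual reading sends any failure to Mann–Whitney.

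**Conclusion.** The point holds in limited form. The plan fixes a data-driven choice between two unadjusted tests with different targets for its primary outcome, visit by visit, and states no volume model that uses the preoperative volume. The planned test remains valid, so this is an improvement that should be made, not a fatal fault.

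The benefit is a fixed effect measure whatever the data look like. The gain in power depends on the correlation: about 5 points at 0.3, 13–14 at 0.5 and 23–24 at 0.7 (0.77, 0.85 and 0.95 against 0.71–0.72), and nothing material at 0. These figures assume log-normal volume, log SD 0.7 and log difference 0.22, with complete data on 138 per arm. They do not cover the case where many hematomas have resolved by 3 months and volumes pile up at zero.

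**What to change.** Delete the Shapiro–Wilk step for volume and pre-set one analysis on one scale, before outcome data are examined.

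- **Primary analysis:** a repeated-measures model for, say, log(volume + 1 mL), with arm, visit, arm-by-visit, preoperative volume and centre. Report the 3-month arm difference with its confidence interval.
- **Covariate:** use the preoperative volume. The day-1 scan is a listed outcome time point, and its order relative to the start of study treatment is not stated. Use it as a covariate only if that scan is confirmed to precede treatment.
- **Sensitivity analysis:** Mann–Whitney with a Hodges–Lehmann interval, which also guards against many zero volumes.
- **mRS and NIHSS:** use the rank test directly, without a normality test.

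The cost is wording only. The data are already collected, SPSS can fit the model, and no extra patients or visits are needed. The downside is that log-scale results must be back-transformed to ratios. The missing equivalence margin has to be dealt with separately.

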### Sample size {14}

In order to estimate the required sample size, the volume change of a primary operated CSDH under the adjuvant therapy forms to be investigated is analogized with the recurrence rates of primary operated and adjuvant embolized or adjuvant drug-treated CSDH in the literature with regard to the target value defined within the primary objective. For example, the MEMBRANE study, which is currently being recruited, assumes a recurrence rate of 10% when combined surgical and interventional therapy is used [11]. In comparison, the work of Hibahashi et al. [27] puts the recurrence rate of CSDH treated with a combination of surgery and medication at around 2%. Based on this, using the *z*-test for independent samples and an error of the first kind (*α* = 0.05), a sample size of 276 patients (138 per group) is required to achieve a power > 0.8 to detect a difference of 8%.

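### The chi-squared test planned for postoperative volume (mL) against revision surgery is not valid on ungrouped volumes, and for NIHSS and mRS it ignores the ordering

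*Protocol article*

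**What the plan says.** Statistical methods {20a} plans three analyses that involve revision surgery.

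- **Between-arm comparison.** Need for revision is listed among the nominal variables compared with Pearson's chi-squared test.
- **Adjusted model.** In addition, "a logistic regression is tested with the revision rate as the dependent variable and the treatment groups and baseline data as independent variables". The covariates are not listed there. The data collection section {18a}/{19} describes what is gathered as "including baseline data (NIHSS, mRS, hematoma volume, patient demographics and characteristics) prior to surgery".
- **Correlation analyses.** Postoperative volume, and the postoperative neurological assessment, are each related to revision "in each case for mixed scaling pairs with the chi-squared test". No categories or cut-points are given, and the text does not say which postoperative visit supplies the volume or the score.

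The Outcomes section {12} measures volume in mL by volumetry at day 1, week 1 and months 1, 2 and 3. Section {20a} itself classes volume as metric and NIHSS and mRS as ordinal.

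**The concern.** Pearson's chi-squared test compares counts across categories. Volume in mL has no categories unless someone makes them, and the plan names the test without doing so. Applied directly, it treats each distinct volume as its own category, and the result no longer reflects any relation between volume and revision. For NIHSS and mRS the categories exist, but the test treats them as unordered labels.

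Timing is a second problem. Imaging continues to month 3, so in a revised patient the later volumes show the effect of the second evacuation. If such volumes enter the analysis, the direction of the association cannot be interpreted.

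What is at stake is the tertiary objective of describing the findings that lead to revision. It bears also on the aim, stated in the Discussion, of identifying which patients suit which therapy. A weaker worry concerns the additional logistic model: few revisions are expected, and its covariate set is open-ended.

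**Working it through.** **Inputs.** From Sample size {14}: the embolization reference "assumes a recurrence rate of 10% when combined surgical and interventional therapy is used"; the tranexamic acid (TXA) reference "puts the recurrence rate of CSDH treated with a combination of surgery and medication at around 2" per cent; and "a sample size of 276 patients (138 per group) is required to achieve a power > 0.8 to detect a difference of 8" per cent, at alpha 0.05. From Trial design {8}: 1:1 allocation.

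**The plan's own figure.** Two-sided z-test, pooled variance under the null, mean rate 0.06:

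n per arm = [1.96·√(2·0.06·0.94) + 0.842·√(0.10·0.90 + 0.02·0.98)]² / 0.08² = [0.658 + 0.279]² / 0.0064 ≈ 137.2, rounded up to 138.

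The total of 276 is reproduced; power at 138 per arm is 0.802.

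**Expected revisions.** 138 × 0.10 + 138 × 0.02 = 13.8 + 2.76 = 16.56, about 17.

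**Chi-squared with all volumes distinct.** Let N be the number of patients, R the number revised and p = R/N. Each volume forms a category of size 1, with expected counts p (revised) and 1 − p (not revised).

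- A revised patient contributes (1 − p)²/p + (1 − p) = (1 − p)/p.
- An unrevised patient contributes p/(1 − p).
- Sum: R(1 − p)/p + (N − R)p/(1 − p) = N(1 − p) + Np = N, on N − 1 degrees of freedom.

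With N = 276 and R = 17 this is 259 + 17 = 276 on 275 df, p = 0.47. The data drop out of the formula. In numerical checks with revised patients' volumes shifted by 0, 1 and 3 SD, chi-squared stayed at 276, while a rank test gave p = 0.13, p = 0.0006 and p < 1e-10.

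**Chi-squared with ties from rounding.** Simulation, 1,000 runs per cell. Assumptions not in the documents: normal volumes, mean 50 mL, SD 20 mL, 6% revised. Entries are the proportion of runs with p < 0.05.

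| Recorded to | Shift in revised patients | Chi-squared | Rank test |
|---|---|---|---|
| 0.1 mL | none | 0.019 | 0.048 |
| 0.1 mL | 0.75 SD | 0.034 | 0.785 |
| 0.1 mL | 1 SD | 0.055 | 0.957 |
| 1 mL | none | 0.117 | 0.050 |
| 1 mL | 0.75 SD | 0.383 | 0.783 |
| 1 mL | 1 SD | 0.605 | 0.944 |

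At fine precision the test is nearly blind. At 1 mL it rejects too often under the null and still has less power than the rank test.

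**Logistic model.** Treatment plus six baseline parameters (an assumed number) leaves 16.56 / 7 = 2.4 events per parameter. Treatment plus one covariate leaves 16.56 / 2 = 8.3; treatment plus two leaves 16.56 / 3 = 5.5. The chance of no revision in the TXA arm is 0.98^138 = 0.062, and ordinary maximum likelihood then has no finite treatment estimate.

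**Main comparison.** In the 2×2 table of arm by revision the smallest expected count is 16.56 / 2 = 8.28, above the usual threshold of 5.

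**The case against.** **The plan does not say that volumes stay ungrouped.** With quartiles, under similar assumptions (6% revised, normal volumes), the test had a type I error of 6.1% and power of 61% and 85% at shifts of 0.75 and 1 SD. That is inefficient but not uninformative. The constant p-value also does not carry over to the integer scores. Both remarks are correct, and they limit the claim of invalidity to ungrouped volume. They do not remove it: the article names a specific test for a variable it calls metric. Grouping would need cut-points, and cut-points chosen after seeing the data invite selection.

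**A reader might infer that the trial's revision results as a whole would mislead.** The documents do not support this. The between-arm test is a 2×2 Pearson test and is sound at the planning rates. The analyses criticised here are additional ones.

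**A reader might also infer that every baseline variable enters the logistic model and badly distorts the treatment effect.** The text says baseline data without saying all of it, and a shorter list could stand in a document not shown. The distortion is small in any case. Against a true log odds ratio of −1.69, simulated means were −1.72 to −1.74 with treatment alone, about −1.78 with six uninformative covariates, and −1.84 to −1.89 with ten, with a standard deviation of about 0.65. Nor do the covariates cause the roughly 6% of trials without a finite estimate: the failure rate was 6.3% with treatment alone and 6.2% with ten covariates. It comes from the chance of no TXA-arm event.

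**Conclusion.** The point holds for the correlation analyses. As written, the chi-squared test on ungrouped volume returns a fixed p of 0.47 when all volumes differ. That result is algebraic and needs no assumption beyond distinct values. With rounded values its error rate and power depend on recording precision; the sizes shown rest on the assumed volume distribution. For NIHSS and mRS the fault is loss of ordering, not a constant result. Leaving the visit open adds the risk of using volumes already changed by the revision.

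The logistic model is a minor point. About 17 revisions follow from the protocol's own rates, too few for an open covariate set. At 10% in both arms there would be about 28, still only about 4 per parameter with seven parameters. The main harm is to the reliability of the covariate effects, not to the treatment estimate.

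The secondary comparison of revision between arms stands.

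**What to change.** 1. In {20a}, replace the chi-squared correlation by a Mann-Whitney test of volume by revision status, or by a logistic regression of revision on volume as a continuous predictor. Do the same for NIHSS and mRS.
2. Fix one early postoperative visit for all patients, before any revision. Day 1 is already an imaging time point for volume. For the scores, the readable text gives week 1 as the earliest follow-up (the schedule table is not readable here). If week 1 is used, state how patients revised before it are handled. Do not pair a last pre-revision value in revised patients with a fixed-visit value in the others, because that mixes time points.
3. Limit the additional logistic model to treatment plus one or two named baseline covariates, or use a penalised fit such as Firth's. The penalised fit also covers the 6% chance of no TXA-arm event; shortening the covariate list alone does not.

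The cost is wording. No new data, visits or patients are needed. The rank test and ordinary logistic regression are methods the section already uses; a Firth fit needs an SPSS extension or R.
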